**Figure 1 F1:**

FAB consort flow diagram.

**Table 1 T1:** Summary of fluoxetine dosing schedule for participants <40 Kg

**Week of trial**	**Dose (per day)**
1	4 mg
2	8 mg
3	14 mg
4	20 mg
5-16	Maintain effective dose
17-20	Wean off medication (at weekly intervals)

**Table 2 T2:** **Summary of fluoxetine dosing schedule for participants** ≥**40 Kg**

**Week of trial**	**Dose (per day)**
1	8 mg
2	14 mg
3	22 mg
4	30 mg
5-16	Maintain effective dose
17-20	Wean off medication (at weekly intervals)

### Participant study visits

#### Baseline, medical and genetic testing

Participants in the study are required to meet the clinician on three occasions, two appointments for baseline assessment and one appointment to study sites for the post-trial assessment. During the first visit the study doctor will take a detailed medical history and conduct a physical examination. For participants who do not have previously documented cognitive testing, the WISC-IV, WNV, or another appropriate measure will be administered by a psychologist during the visit. In addition, consent will be obtained from the parents and a cheek-brush sample will be collected for genetic analysis of the serotonin transporter gene (*SLC6A4*). The second visit will involve a confirmation of the participant’s ASD diagnosis by a trained psychologist using the ADI-R and DSM-IV-TR criteria.

During either of these baseline visits, baseline ratings will be obtained for the CYBOCS-PDD, RBS-R, SCAS-parent version, and the ABC-community version. Baseline ratings for the CGI-R will be obtained by the study doctor, psychologist, and/or research assistant. In addition, participant’s levels of anxiety, anger/aggression, sadness/depression, excitability/overexcited, and ADHD were rated on a scale of 0 to 2 by the study doctor, psychologist, and/or research assistant. Following the second visit, the participant is randomized and study medication commencement is arranged.

#### Post-treatment assessments

At the completion of the 16-week treatment period, the participant and their parent(s) will be asked to return to the hospital for another study visit. During this visit ratings will be obtained for the CYBOCS-PDD, RBS-R, SCAS-parent version, ABC-community version, and the CGI. The participant's levels of anxiety, anger/aggression, sadness/depression, excitability/overexcited, and AD/HD were rated on a scale of 0 to 2 by the study doctor, psychologist, and/or research assistant. The participant is then weaned off the study medication over a four-week period and monitored weekly by either the research assistant or the study doctor.

#### Treatment delivery

The dosage schedule for the study medication, summarized in Tables 1 and 2, is based on previous research that highlights the importance of using lower doses and titrating doses slowly when treating children and adolescents with autism [13,28,29]. Dosages will be monitored using medication diaries provided to participants and their parents by the treating clinician. Participants will be given three medication diaries that outline the amount of medication to be taken at given periods: ‘Diary 1’ for weeks 1 to 4, in which titration levels are increased; ‘Diary 2’ for weeks 5 to 16, in which medication dosages are consistent and maintained; and ‘Diary 3’ for weeks 17 to 22, in which medication is tapered. Parents are required to return each booklet at the required interval to monitor medication compliance.

### Monitoring, governance and withdrawal

#### Quality assurance and training

Trial psychologists who will carry out the assessments will have the required experience and training to administer psychometric testing and will undertake training to obtain a research accreditation for the administration of the ADI-R if they do not already have this training. Trial doctors (pediatricians or psychiatry registrars) will be supervised by a chief investigator (pediatrician or psychiatrist) as well as a trial coordinator at each site to ensure protocol compliance.

#### Adverse events and safety monitoring

A medical history and physical examination will be conducted prior to the commencement of the study. This will assist in the interpretation of adverse events if they occur during the study. Monitoring for adverse events will occur by phone consultations on a weekly basis during tapering up and weaning down of the study medication. During weeks 4 to 15, participants will be monitored on a fortnightly basis. All adverse events reported by the participant and/or caregiver will be thoroughly evaluated and appropriate measures taken as per trial protocol guidelines. The nature of each adverse event, time of onset, duration, severity, and relationship to treatment will be established and recorded. Details of any changes to the dosage schedule or any corrective treatment will be recorded. All serious adverse events will be reported to the relevant Human Research Ethics Committee and Adverse Drug Reaction Committee, and well as the study Independent Data Safety Monitoring Committee (DSMC). The clinical trials coordinator will also be available to assist if necessary. Participants are able to contact coordinators at any given time should they be concerned about potential adverse side effects.

#### Patient completion and withdrawal

Subjects will be considered to have finished the study upon completion of 16 weeks of the study medication. Premature termination of the study drug will be defined as completing less than 16 weeks of treatment. Even if the study drug is terminated, every effort will be made by the investigator to maintain data collection until study completion. A patient may withdraw (or be withdrawn) from treatment prematurely because of significant adverse events, or a patient or caregiver decision to discontinue the treatment.

### Data collection

#### Case report forms (CRF)

All study data will be captured on a CRF. The CRF will contain the patient’s study number, date of each consultation (including phone consultations), results of pre and post assessments, and adverse events, and include medications that participants may be taking that are not on the exclusion list.

#### Web-based database

An online database will be developed for the trial, with data entry occurring at each site. Original CRFs will be used when entering information into the computer database, by the study coordinator at each site.

#### Serotonin transporter gene

To determine a relationship between an individual’s serotonin transporter genotype and response to treatment with fluoxetine compared to placebo in children and adolescents with autism (Secondary Aim 2 of the study), genetic samples will be collected and sent from study sites and de-identified prior to processing at the Bruce Lefroy Centre, Murdoch Children’s Research Institute. Samples will be collected by a cheek brush and genotypes determined by polymerase chain reaction (PCR using Bio-Rad iCycler, California) and gel electrophoresis analysis.

#### Sample size

Previous data from 172 medication-free children with ASD showed a mean total score of 14.4, with a standard deviation (SD) of 3.86 on the CYBOCS-PDD [27]. Based on the study investigators’ clinical experience in the management of children with ASD, it was thought that a difference of 2 on the CYBOCS-PDD would represent a clinically important improvement in repetitive behaviors (approximately 0.5 of a standard deviation). In order to find an effect size of 0.5 (corresponding to a difference of 2 on the CYBOCS-PDD based on a standard deviation of 3.8) with 80% power and a two-sided alpha of 0.05 requires a sample size of 64 per treatment group. Allowing for a 15% attrition rate, we therefore plan to recruit 73 participants per treatment group for a total of 146 participants.

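### 73 per group does not allow for 15% attrition on the required 64: about 62 would remain, an arithmetic slip with little effect on power

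*Protocol article*

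**What the plan says.** Everything needed is in the protocol article. The Sample size section takes its variability from earlier data on medication-free children with ASD, which "showed a mean total score of 14.4, with a standard deviation (SD) of 3.86 on the CYBOCS-PDD". It names a difference of 2 points as clinically important and describes this as "approximately 0.5 of a standard deviation". The calculation is then set for an effect size of 0.5, "corresponding to a difference of 2 on the CYBOCS-PDD based on a standard deviation of 3.8", which "with 80% power and a two-sided alpha of 0.05 requires a sample size of 64 per treatment group". The last step is the recruitment target: "Allowing for a 15% attrition rate, we therefore plan to recruit 73 participants per treatment group for a total of 146 participants".

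Three other places bear on this. Enrollment and randomization sets 1:1 allocation. Statistical analysis restricts the analysis to participants who have outcome data. Primary outcome compares the groups with an unadjusted linear regression, which for two groups is the two-sample t-test.

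**The concern.** The evaluable number, the attrition rate and the recruitment number cannot all be right. An attrition rate is a share of those recruited, so the number recruited, reduced by 15%, should return at least 64. It does not. Because the analysis uses only participants with outcome data and the primary model is unadjusted, nothing else in the stated plan makes up the difference.

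At stake is the trial's only sample-size justification, in an article that criticises earlier trials as too small and calls for an adequately powered one. Someone who later checks whether the trial met its target would find that it missed 64 per group even if attrition ran exactly as planned.

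A smaller matter lies in the same lines. The effect size of 0.5, the difference of 2 and the SD of 3.8 are presented as equivalent, and the SD appears as both 3.86 and 3.8.

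**Working it through.** **Inputs** (all from Sample size unless noted): two-sided alpha 0.05; power 80%; effect size d = 0.5; target difference 2 points; SD 3.86 (source data) and 3.8 (calculation); 64 evaluable per group; attrition 15%; 73 recruited per group, 146 in total; 1:1 allocation (Enrollment and randomization); unadjusted comparison of two means (Primary outcome).

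**Step 1. Reproduce the 64.** The normal approximation is n = 2(1.960 + 0.842)²/d² = 2 x 7.85/0.25 = 62.8, so 63 per group. The exact t-test calculation gives 63.77, so 64. The stated 64 is correct for d = 0.5.

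**Step 2. Reproduce the 73.** Inflation for a loss fraction a is n/(1 - a).
- 64/0.85 = 75.3, so 76 per group and 152 in total. The stated figures are 3 per group and 6 overall too low.
- In the other direction, 73 x 0.85 = 62.05, so about 62 per group remain.
- The loss that 73 can absorb is 1 - 64/73 = 12.3%.
- Multiplying instead of dividing comes close to 73: 64 x 1.15 = 73.6 (73 if truncated), or 63 x 1.15 = 72.45 (73 if rounded up). The article does not say how 73 was reached, so this is only a possible explanation.

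**Step 3. Relate effect size, difference and SD.** 2/3.8 = 0.526 and 2/3.86 = 0.518. Both round to 0.5 at one decimal, and both are larger than 0.5. Sizing for 0.5 therefore asks for more participants than the 2-point target needs.

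**Step 4. Power with 62 per group.** Two-sided t-test, 2 x 62 - 2 = 122 degrees of freedom, noncentrality d x √(62/2) = d x 5.568.

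| Target | d | Noncentrality | Power at 62 per group | Evaluable n per group for 80% | Recruited n per group at 15% loss |
|---|---|---|---|---|---|
| Effect size as stated | 0.500 | 2.784 | 78.9% | 64 | 76 |
| 2 points, SD 3.86 | 0.518 | 2.885 | 81.7% | 60 | 60/0.85 = 70.6, so 71 |
| 2 points, SD 3.8 | 0.526 | 2.930 | 82.8% | 58 | 58/0.85 = 68.2, so 69 |

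For comparison, 64 per group at d = 0.5 gives 80.1%. The normal approximation at 62 per group and d = 0.5 gives 79.5%.

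The slip therefore costs about one percentage point of power at d = 0.5. For a difference of 2 points, the planned 73 per group exceeds the correctly inflated number at either SD.

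**The case against.** The strongest reply is that nothing of substance is lost. The difference the investigators care about is 2 points, and 146 recruits with 15% loss give more than 80% power for it at either SD in the text. Rounding 0.518 or 0.526 down to 0.5 is conservative, and the article signals the rounding when it calls the difference "approximately 0.5 of a standard deviation". This stands, and it settles the size of the point. It does not make 73 the right answer to the calculation as written, which is set at 0.5 and requires 64.

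A second reply is that loss of outcome data may be lower than 15%. Patient completion and withdrawal says that efforts will be made to keep collecting data after study drug is stopped, so some who discontinue may still have a 16-week score. That may soften the effect in practice, but 15% is the allowance the plan chose, and the arithmetic has to be consistent with it.

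Two stronger readings are tempting, and the document supports neither. A reader might add the SD mismatch to the attrition error and infer a compounded loss of power. In fact the two work in opposite directions, and the rounding more than offsets the slip. A reader might also infer that the target is unclear, because 0.5 x 3.8 = 1.9 points. The article states a difference of 2 points twice, the first time as the clinically important difference, and 1.9 appears nowhere in it.

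**Conclusion.** Wrong as written, and minor. At the planned 15% attrition, 73 per group leaves about 62 and not 64. Holding 64 would take 76 per group (152 in total), and 73 covers about 12%. Power at an effect size of 0.5 is then about 79% against the stated 80%. For 2 points it is about 82% at SD 3.86 and 83% at SD 3.8, so the document does not support calling the trial materially underpowered.

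This rests on three assumptions: attrition means having no 16-week primary outcome, losses are equal in the two groups, and the SD from the earlier data applies to the 16-week score. The attrition arithmetic itself depends only on the first. The use of 3.8 beside 3.86, with 2 points equated to exactly 0.5, is a wording matter with no cost to the design.

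**What to change.** Keep 146 and correct the statement in one of two ways.

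- Restate the power, for example: *73 per group with 15% attrition leaves about 62 evaluable per group, giving 79% power for a standardised difference of 0.5, or 82% for a 2-point difference at SD 3.86.*
- Or keep 64 as the evaluable target and state that 73 per group allows for about 12% attrition.

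As a wording note, use the source SD of 3.86 throughout and give 2/3.86 as about 0.52.

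The cost is a sentence or two, and one stated figure becomes slightly less favourable. Design, analysis and recruitment are unchanged. If the sponsor prefers to keep 64 evaluable, 15% attrition and 80% power at 0.5 all as stated, the price is 152 recruits, 6 more than planned; the power for the 2-point difference does not require this.

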#### Statistical analysis

Analysis will be performed on an intention-to-treat basis, including all participants with outcomes data available.

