**Methods/Design:**

The FAB study is a multicenter, double-blinded, randomized controlled trial, funded by the Australian Government’s National Health and Medical Research Council (NHMRC) grant. Participants will be aged between 7.5 and 17 years with a confirmed diagnosis of ASD. Eligible participants will be randomized to either placebo or fluoxetine for a 16-week period. Medication will be titrated over the first four weeks. Reponses to medication will be monitored fortnightly using the Clinical Global Impressions Scale (CGI). The primary outcome measure is the Children’s Yale-Brown Obsessive Compulsive Scale-Modified for Pervasive Developmental Disorders (CYBOCS-PDD), administered at baseline and 16 weeks. Secondary outcome measures include the Aberrant Behaviour Scale (ABC), the Spence Children’s Anxiety Scale Parent Report (SCAS-P), and the Repetitive Behaviors Scale (RBS-R), measured at baseline and 16 weeks. Participants will be invited to undergo genetic testing for *SLC6A4* allele variants using a cheek swab. Continuous outcomes, including the primary outcome will be compared between the active and placebo groups using unadjusted linear regression. Binary outcomes will be compared using unadjusted logistic regression.

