#### Primary outcome

The primary outcome (total score on the CYBOCS-PDD at 16 weeks) will be summarized by mean and standard deviation (SD) treatment group, with the comparison between active and placebo presented as the difference in means and the 95% confidence interval (CI), obtained using an unadjusted linear regression model. As a sensitivity analysis, the regression models will also be adjusted for pre-trial CYBOCS-PDD score, age, and IQ at baseline.

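### The primary analysis is labelled intention-to-treat but is an available-case comparison unadjusted for baseline, so it could be biased in either direction if loss to week 16 selects differently in the two arms

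*Protocol article*

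**What the plan says.** Protocol article, Statistical analysis: "Analysis will be performed on an intention-to-treat basis, including all participants with outcomes data available".

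Primary outcome: the difference in mean week-16 CYBOCS-PDD total score is "obtained using an unadjusted linear regression model". The same section adds: "As a sensitivity analysis, the regression models will also be adjusted for pre-trial CYBOCS-PDD score, age, and IQ at baseline". Secondary outcomes follows the same order, with the unadjusted model first and the adjusted model as sensitivity analysis.

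Baseline and follow-up measures: the primary score is taken at baseline and at week 16, with nothing in between.

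Sample size: "Allowing for a 15% attrition rate, we therefore plan to recruit 73 participants per treatment group for a total of 146 participants".

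Patient completion and withdrawal: "A patient may withdraw (or be withdrawn) from treatment prematurely because of significant adverse events", or by patient or caregiver decision. The same section says: "Even if the study drug is terminated, every effort will be made by the investigator to maintain data collection until study completion".

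**The concern.** Three stated choices combine. Only participants with a week-16 score are analysed. With no intermediate CYBOCS-PDD, a participant without that score contributes nothing to the primary comparison, not even a baseline value. And the primary model does not condition on baseline severity, although that score is collected and a model using it is already planned.

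The sponsor itself allows for about one participant in seven being lost. The reasons for loss could differ between arms: the Background mentions suggested dose-related harms of SSRIs such as agitation and aggression, and placebo participants may leave for lack of benefit. If those lost differ from those retained, and differ in one arm more than in the other, the comparison of the retained participants is no longer the randomized comparison. The intention-to-treat label would then suggest more protection than the analysis gives.

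**Working it through.** **The plan's own figure.** Inputs from Sample size: effect size 0.5, 80% power, two-sided alpha 0.05. Normal approximation: n = 2 × (1.960 + 0.842)² / 0.5² = 62.8, so 63 per group. The two-sample t-test gives 63.8, so 64, as stated. Of 73 recruited per group, 15% attrition leaves 73 × 0.85 = 62.05, so about 62 analysed and 11 not.

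**Condition for no bias.** In each arm let p be the missing fraction and D the mean of the missing minus the mean of the observed. The mean of all randomized participants is (1 − p) × observed + p × missing = observed + p × D. With F for fluoxetine and P for placebo:

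bias of the available-case difference = −(pF × DF − pP × DP)

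Lower scores are better, so a negative bias favours fluoxetine. The bias is zero exactly when the two products are equal.

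**Assumed scenarios.** The documents give neither p by arm nor D, so these values are assumptions.

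| Missing F / P | DF | DP | Bias (points) |
|---|---|---|---|
| 20% / 10% | 0 | 0 | 0 |
| 15% / 15% | 2 | 2 | 0.15×2 − 0.15×2 = 0 |
| 15% / 15% | 2 to 4 | 0 | −0.3 to −0.6 |
| 15% / 15% | 0 | 2 to 4 | +0.3 to +0.6 |
| 20% / 10% | 2 to 4 | 2 to 4 | −0.2 to −0.4 |

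Against the 2-point target, 0.3 to 0.6 is 15% to 30%. With 62 per arm and SD 3.8, the standard error is 3.8 × √(2/62) = 0.68, so this is 0.44 to 0.88 standard errors. If the true effect were zero, a shift of that size would raise the two-sided 5% error rate to about 7% to 14%.

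**What baseline adjustment changes.** A simulation of 4 million participants used SD 3.8, a true difference of −2, and adjustment for baseline score only. Assumed: baseline-to-week-16 correlation of 0.4, 0.6 or 0.8, and log-odds of loss rising by 1 per SD of severity. Zero means within 0.01.

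| Loss depends on | Missing F / P | Bias, unadjusted (0.4, 0.6, 0.8) | Bias, adjusted (0.4, 0.6, 0.8) |
|---|---|---|---|
| Baseline, same in both arms | 15% / 15% | 0 | 0 |
| Baseline, fluoxetine only | 15% / 15% | −0.20, −0.30, −0.40 | 0 |
| Baseline, both arms | 20% / 10% | −0.13, −0.18, −0.24 | 0 |
| Week-16 score, same in both arms | 15% / 15% | 0 | 0 |
| Week-16 score, fluoxetine only | 15% / 15% | about −0.50 | −0.43, −0.33, −0.19 |

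Adjustment removes bias from loss that depends on baseline. It reduces, but does not remove, bias from loss that depends on the outcome in one arm.

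**Precision.** Adjusting for a baseline score with correlation r multiplies the residual variance by 1 − r²: 0.84, 0.64 and 0.36 at the three assumed correlations.

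**The case against.** The strongest reply is that the article condenses a fuller plan. Imputation models, auxiliary variables and tipping-point analyses commonly sit in a statistical analysis plan that is not shown, so their absence here is no fault. That stands. What remains is what the article fixes itself: the analysis set, and an unadjusted model as primary.

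A reader might go further in four ways that the documents do not support.

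- *That the analysis is valid only if scores are missing completely at random.* This is too strong. The first two rows of the scenario table show zero bias with loss that depends on arm alone, and with equal selection in both arms.
- *That baseline severity is ignored.* A model adjusted for baseline score, age and IQ is planned. It is ranked as a sensitivity analysis, and it too uses only participants with outcome data.
- *That those who stop fluoxetine leave the analysis.* The withdrawal text concerns treatment, and the section intends data collection to continue afterwards. A participant who stops the drug but attends at week 16 is analysed. The 15% need not equal treatment discontinuation. It is, however, the sponsor's own allowance for attrition despite that intention.
- *That the bias favours fluoxetine.* No arm-specific dropout rates or scores of non-completers are given. Agitation need not mean a worse CYBOCS-PDD score, and loss from placebo for lack of benefit would reverse the sign.

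One practical caution also stands. The abstract says that responses are "monitored fortnightly using the Clinical Global Impressions Scale (CGI", but the body places CGI ratings at baseline and week 16 and describes the interim phone contacts as dosage, side-effect and adverse-event monitoring. Interim CGI cannot be taken for granted as an imputation predictor.

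**Conclusion.** The point holds in limited form. The article fixes an available-case primary comparison under an intention-to-treat label and ranks the better-protected adjusted model below it. The primary estimate is unbiased only when selection, measured as missing fraction times missing-minus-observed mean, is equal in the two arms. Otherwise it could be biased in either direction. The 0.3 to 0.6 points (15% to 30% of the target difference) rests on the assumed 15% loss per arm, with those lost from one arm 2 to 4 points worse and those lost from the other no different. It illustrates what is possible and is not a forecast. This does not invalidate the design, but the choice is worth changing because a better one is already in the plan.

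**What to change.** 1. Make the model adjusted for baseline CYBOCS-PDD, age and IQ the primary analysis, and add site, which is a stratification factor missing from it. If the model is correctly specified, the condition relaxes to missing at random given arm and those covariates. Precision improves to the extent that baseline predicts week 16. Keep the unadjusted comparison as a sensitivity analysis.
2. Call the present analysis set available-case, analysed as randomized, and reserve intention-to-treat for all randomized participants.
3. As a supporting analysis, include all randomized participants by multiple imputation with a small set of predictors: baseline scores, adverse events, dose changes, and interim CGI only if it is actually recorded. With about 73 per arm, a long predictor list would be unstable.
4. Add a delta-adjusted analysis that shifts imputed scores in each arm in turn, for example by 0 to 4 points, so that departures in both directions are covered.

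Items 1 and 2 change wording and the order of analyses, and use data already planned. Items 3 and 4 cost modest extra analysis and rely on an imputation model, which the delta analysis probes. Trial status reports recruitment still open at submission, so the change could be documented before unblinding.
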